### Randomised treatment allocation, blinding and sample-size estimation

Patients are randomly allocated to either the preemptive or the postoperative treatment group. These two groups are each divided into two arms. Preemptive group patients receive etoricoxib prior to surgery and either etoricoxib again or placebo postoperatively. Postoperative group patients receive placebo prior to surgery and either placebo again or etoricoxib after surgery (2 × 2 factorial study design, Figure 1). The randomisation procedure into the two study arms was performed by the Institute of Medical Information Technology, Biometry and Epidemiology, University of Munich, Germany. The biometricians compiled an allocation list which was the basis for the pharmacists to prepare sequentially numbered envelopes containing two boxes of study medication for pre- and postoperative use. The boxes contained either a 120 mg dose of etoricoxibe or an equivalent placebo pill. After inclusion into the trial, the study physician assigned the content of the lowest numbered envelope to the patient. Neither the patient nor the study physician knew about the content of the boxes, the pills were not distinguishable. This procedure assured a complete blinding.

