### Interventions

Patients are randomly allocated to either the preemptive or the postoperative treatment group. Preemptive group patients get etoricoxib 120 mg p.o. prior to surgery (day 0). After surgical intervention, depending on their respective allocation, patients receive either etoricoxib 120 mg p.o. or placebo for the next three postoperative days (day 1-3). Postoperative group patients get placebo prior to surgery and continue afterwards with either placebo or etoricoxib 120 mg p.o. for three postoperative days (2 × 2 factorial study design, Figure 1). All patients will receive standardised morphine (patient controlled analgesia PCA; bolus 2 mg; interval 10 min; max dosage 30 mg/4 h). Patients, study physicians and contributing hospital staff are blinded regarding the treatment group allocation.

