#### Secondary outcome measure

- Baseline personal situation on the DGSS (German Society for the Study of Pain) validated pain questionnaire [24], comprising inter alia the German versions of questionnaires assessing demographic data, pain variables (e. g. pain sites, temporal characteristics, duration, intensity), pain associated symptoms, affective and sensory qualities of pain (adjective list by Geissner, SES), pain relieving and intensifying factors, previous pain treatment procedures, pain-related disability (Pain Disability Index), depression (Centre for Epidemiological Studies Depression Test CES-D), comorbid conditions, social factors (educational level, occupation, retirement status, compensation or litigation status, disability for work), health related quality of life (SF-36).

- Systematic quantitative sensory testing (QST). The detailed QST protocol including reference data is reported elsewhere [25]. In brief, the following testing procedures were performed:

a) **Thermal Testing **comprising cold and warm detection thresholds (CDT, WDT), paradoxical heat sensations (PHS) during the thermal sensory limen procedure (TSL) of alternating warm and cold stimuli and cold and heat pain thresholds (CPT, HPT);

b) **Mechanical Testing **comprising mechanical detection thresholds (MDT), mechanical pain thresholds (MPT), mechanical pain sensitivity (MPS), dynamic mechanical allodynia (DMA), the wind-up ratio (WUR), vibration detection thresholds (VDT) and pressure pain thresholds (PPT).

- Pain intensity (visual analogue scale)

- Overall morphine consumption

- Side effects (documentation according to ICH - GCP Guidelines)

- Genetic polymorphisms: the metabolic profile of etoricoxib involves cytochrome P450-dependent hydroxylation and oxidation as primary clearance pathways [26]. Different genotypes might either be the reason for individually different analgesic needs or be considered as a risk factor for side effects [27]. Similar mechanisms have been described for the use of opioids and so called multidrug resistance proteins (MDR) [28]. We therefore collected EDTA-blood samples from all patients to analyse the different expression of genotypes.

For time points please refer to Figure 1.

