### Data Analysis

Descriptive analysis of the study population (including means, standard deviations, median and frequencies) will be made for all parameters.

Main outcome measures will be analysed with a 2 × 2 factorial ANOVA. Independent variables are time point of medication uptake and allocated study arm, dependent variable is the cumulative morphine consumption within 48 hours postoperatively.

Secondary outcome measures (QST, pain intensity) will be analysed equivalent, taking into account the test interval (repeated measurement ANOVA). ANOVA will be adjusted according to Bonferroni using t-test for post-hoc confirmation of significant alterations.

Ordinal scaled data will be analysed with Kruskal Wallis test confirming significance with chi2 test.

For analyses of associative coherence we will use Spearman's correlations coefficient, Wilcoxon-test or Kruskal Wallis test. All reports will be performed according intention-to treat analysis.

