## Etoricoxib

Several COX-2-inhibitors have been shown to be effective treating postoperative pain [31-33]. Data for the use of etoricoxib seem to be promising; however, existing results describing preemptive and postoperative effects remain heterogeneous [34-36]. Etoricoxib is a COX-2-selective NSAID which is approached for treatment of osteoarthritis, rheumatoid arthritis, acute gouty arthritis and Morbus Bechterew. Numerous studies indicated that etoricoxib has similar efficacy as traditional, unselective NSAIDs have. It does not seem to elevate the risk of severe side effects, i.e. in special vascular events [29,37]. The rates of thrombotic cardiovascular events in 34.000 patients with arthritis on etoricoxib were similar to those in patients with long-term use of diclofenac [29]. Ex vivo whole-blood assays after multiple oral doses of etoricoxib showed no important effects on bleeding time or platelet aggregation [38]. Consequently, these drugs do not carry the risk of blocking surgical interventions.

Additionally, etoricoxib demonstrated superior safety in gastrointestinal toxicity due to its high selective COX-2 inhibition that is observed with its use. Other NSAID-associated effects, including renal adverse effects, appear to be similar to those of other traditional NSAIDs [20].

The pharmacokinetic evaluation of etoricoxib indicates a moderate rate of absorption and a t1/2 of approximately 20 hours that enables once-daily dosing [20].

We have chosen etoricoxib as verum treatment due to the presented pharmacologic properties such as our own clinical experience dealing with. Drug approval for peri- and postoperative setting has not yet been authorised.

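### The intention-to-treat rule for all reports, read literally, also covers side effects and so modestly dilutes the safety comparison for postoperative etoricoxib

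*Protocol article*

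**What the plan says.** The protocol article fixes one analysis population for everything it reports: "All reports will be performed according intention-to treat analysis" (Data Analysis). No exception is stated. Side effects are among the secondary outcomes, with only a documentation standard attached: "Side effects (documentation according to ICH - GCP Guidelines" (Secondary outcome measure). They also fall under the general promise "Descriptive analysis of the study population (including means, standard deviations, median and frequencies) will be made for all parameters" (Data Analysis). The inferential plan for secondary outcomes names other variables: "Secondary outcome measures (QST, pain intensity) will be analysed equivalent".

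On timing, each patient is assigned both treatments at once, from "sequentially numbered envelopes containing two boxes of study medication for pre- and postoperative use" (Randomised treatment allocation, blinding and sample-size estimation). The preoperative tablet is given on day 0. The postoperative tablets follow after surgery: "patients receive either etoricoxib 120 mg p.o. or placebo for the next three postoperative days (day 1-3" (Interventions).

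**The concern.** Allocation to the postoperative treatment happens before surgery, and the first postoperative tablet comes on day 1, by mouth, after a laparotomy or thoracotomy. Some patients may never take it, for example because they cannot swallow, vomit or withdraw. Under the stated rule they remain in the group they were allocated to, so unexposed patients are counted as exposed to postoperative etoricoxib.

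For a superiority comparison of morphine consumption this is the usual cautious choice. For side effects the same pull towards no difference works the other way, because it makes an excess on etoricoxib look smaller. The side-effect table matters here because the Etoricoxib section says that the drug is not yet approved for the peri- and postoperative setting.

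This is a rule the article states, not a detail it leaves out. A later analysis plan that defined a safety set by treatment received would contradict the sentence as written.

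**Working it through.** The article gives no side-effect rate, no rate of non-intake and no power for safety, so there is no figure of its own to reproduce. The size below is an illustration.

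**Inputs**
- Group size: 60 per level of the postoperative factor (sample-size section: 30 in each of four arms).
- Share never taking a postoperative tablet, f: not stated. I assume 10% and show 4% to 20%. The article's 10% is a general drop-out allowance, set above the 4% drop-out in the reference trial. It is only a stand-in for non-intake.
- Side-effect risk after the first postoperative tablet: assumed 15% on placebo and 35% on etoricoxib.
- Two-sided alpha of 0.05. The article gives 0.05 without stating sidedness.

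**Step 1: dilution of the difference.** Allocated patients who never take etoricoxib are given the placebo risk:

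risk by allocation = (1 − f) × 0.35 + f × 0.15

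At f = 10% this is 0.315 + 0.015 = 0.33. The difference is 0.33 − 0.15 = 18 points instead of 20. In general the difference shrinks by the factor (1 − f).

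**Step 2: power.** With n per group, h = 2·arcsin√p₁ − 2·arcsin√p₀ and power = Φ(h·√(n/2) − 1.96).
- By allocation, 0.15 vs 0.33, n = 60: h = 0.428, h·√30 = 2.347, power Φ(0.387) = 65%.
- Takers only, 0.15 vs 0.35, n = 54 (60 × 0.90): h = 0.471, h·√27 = 2.446, power Φ(0.486) = 69%.

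**Step 3: range over f**

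| Never take the tablet | Difference by allocation | Power by allocation (n = 60) | Power in takers, difference 20 points |
|---|---|---|---|
| 4% | 19.2 points | 70% | 71% (n = 57.6) |
| 10% | 18.0 points | 65% | 69% (n = 54) |
| 20% | 16.0 points | 56% | 64% (n = 48) |

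**Step 4: a smaller assumed effect.** With 10% vs 25% and f = 10%, the difference by allocation is 0.9 × 15 = 13.5 points instead of 15, and the risk ratio falls from 2.50 to 2.35 (0.235/0.10).

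The bias always runs towards no difference, in proportion to non-intake. It weakens a signal without removing it.

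**The case against.** The strongest reply is that little follows from the sentence. Side effects are not named for any test, so power describes an analysis that the article does not plan. Safety sets, treatment-emergent definitions and on-treatment windows are things a condensed article may leave to the full protocol or analysis plan. Descriptive frequencies by arm do not stop anyone reporting onset dates. All of this stands: the power figures are illustrative, and the absence of those definitions is not a finding. The wording of the rule itself also stands, since it covers all reports and side effects are one of the reported outcomes.

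A reader might infer something stronger: that events on the day of surgery are also counted for the postoperative factor, before either group has had a postoperative tablet, and that harm is thereby masked. The documents do not support this. Intention-to-treat fixes which patients are analysed and in which arm. It does not fix which dates count, and a window starting at the first postoperative tablet is compatible with it. The article states no event window, and it refers to Figure 1 for time points, which is not available here.

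The large losses belong to that unstated window. Suppose 20% or 50% of both groups had a day-0 event that was counted. With 10% non-takers, the difference by allocation would fall to 0.9 × 0.8 × 20 = 14.4 points or 0.9 × 0.5 × 20 = 9.0 points, with 37% or 17% power. Restricting to takers while still counting those events would give only 40% or 19%. So the intention-to-treat sentence is not what drives that loss.

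**Conclusion.** The point holds as a minor one. By its wording, the rule puts side effects under allocation, so patients who never take a postoperative tablet count as exposed to postoperative etoricoxib, and any difference is modestly diluted. Assuming 15% vs 35% and 10% non-takers, the cost is 2 percentage points of difference (20 to 18) and about 4 points of power (69% to 65%). With 4% to 20% non-takers, the difference lost is 0.8 to 4 points. These sizes rest on assumed rates, and the 10% is a borrowed drop-out allowance.

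To say that the rule masks harm would go too far: an excess would be somewhat understated but still visible to the same broad degree.

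**What to change.** In Data Analysis, limit the intention-to-treat sentence to the efficacy outcomes and add a sentence for side effects:
- Report them in patients who took study medication, grouped by the treatment taken.
- For the preoperative factor, count from the preoperative tablet.
- For the postoperative factor, count from the first postoperative tablet, active or placebo, among those who took it.
- Keep the by-allocation table as a supplement.

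The cost is about two sentences, plus use of tablet intake and onset dates. A few patients leave the safety denominator. Because the pills are indistinguishable and staff and patients are blinded, failure to take the first postoperative tablet is unlikely to depend on which one was allocated. The comparison among takers therefore stays essentially randomised.

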### Data entry

Data entry is done with SPSS statistical software system (SPSS Inc., Chicago, IL; version 15.0). Data analysis will be done with SAS/STAT^® ^Software (SAS Institute Inc., Cary, NC, USA). All data entry will be carried out twice.

### Monitoring

Internal and external audits will be held in order to assure quality standards according to ICH-GCP guidelines, the Declaration of Helsinki and governmental standards.

## Discussion

To our knowledge, the EPPA trial is the first clinical study to investigate the preemptive analgesic effect of etoricoxib on the cumulative postoperative morphine consumption applying a 2 × 2 factorial study design. In addition, our protocol takes into account individual sensoric perception of the skin as well as genetically different polymorphisms regarding the drug action.

Inclusion and exclusion criteria were deployed pragmatically in order to facilitate screening and recruitment. Exclusion criteria (besides standard items such as pregnancy or contraindications to the study medication) are either disease interfering with the patients' sensory perception or with expected side effects or possible harm related to etoricoxib. Our inclusion and exclusion criteria are based on further trials and according to the summary of product information [29,30]

## Etoricoxib

Several COX-2-inhibitors have been shown to be effective treating postoperative pain [31-33]. Data for the use of etoricoxib seem to be promising; however, existing results describing preemptive and postoperative effects remain heterogeneous [34-36]. Etoricoxib is a COX-2-selective NSAID which is approached for treatment of osteoarthritis, rheumatoid arthritis, acute gouty arthritis and Morbus Bechterew. Numerous studies indicated that etoricoxib has similar efficacy as traditional, unselective NSAIDs have. It does not seem to elevate the risk of severe side effects, i.e. in special vascular events [29,37]. The rates of thrombotic cardiovascular events in 34.000 patients with arthritis on etoricoxib were similar to those in patients with long-term use of diclofenac [29]. Ex vivo whole-blood assays after multiple oral doses of etoricoxib showed no important effects on bleeding time or platelet aggregation [38]. Consequently, these drugs do not carry the risk of blocking surgical interventions.

Additionally, etoricoxib demonstrated superior safety in gastrointestinal toxicity due to its high selective COX-2 inhibition that is observed with its use. Other NSAID-associated effects, including renal adverse effects, appear to be similar to those of other traditional NSAIDs [20].

The pharmacokinetic evaluation of etoricoxib indicates a moderate rate of absorption and a t1/2 of approximately 20 hours that enables once-daily dosing [20].

We have chosen etoricoxib as verum treatment due to the presented pharmacologic properties such as our own clinical experience dealing with. Drug approval for peri- and postoperative setting has not yet been authorised.

## Quantitative sensory testing

Postoperative pain involves not only peripheral mechanisms, most notably the sensitization of nociceptors due to inflammation, but also secondary central mechanisms, including hyperexcitability of nociceptive neurons (i.e., central sensitization, [39,40]). These processes play a major role in postoperative pain, including spontaneous pain and allodynia or hyperalgesia. In particular, peripheral sensitization would explain the hyperalgesia observed at the incision site (primary hyperalgesia), whereas central sensitization would provide a major mechanism of secondary hyperalgesia at distant noninflammatory sites [41-43]; thus indicating a possible pathway for the occurrence of prevalent pain.

From a clinical perspective, preoperative measurement of sensoric perception may have some predictive value regarding postoperative pain and, therefore, may also predict perioperative analgesic requirement [44]. Martinez et al. showed that preoperative heat hyperalgesia directly correlated with postoperative morphine consumption after total knee arthroplasty [43]. These results are in agreement with those of previous studies on the prognostic value of preoperative pain for immediate postoperative pain intensity with other types of surgery [45,46]. Postoperative segmental secondary hyperalgesia was detected in patients undergoing different types of surgical interventions [47-49]. Several central and peripheral pathophysiological actions play a role in the development of acute and chronic postoperative pain. Quantitative sensory testing (QST) allows precise characterization of sensory deficits and painful symptoms and may offer additional information on the pathophysiology of postoperative pain. A follow-up sensory testing in our trial is performed six months after intervention. Therefore, we will be able to provide information regarding long-term sensitisation after surgery, too. Taken together, we will be able to evaluate possible predictive factors related to patients' individual sensoric perception that may influence the intensity of postoperative pain and analgesic consumption such as characteristics that might predict or prevent chronification.

## Genetics

Genetic polymorphisms in P-glycoprotein (P-gp), a membrane-localised transporter codified by the gene MDR1 and Cytochrome P450 (CYP) genes, are involved in drug metabolism and often account for variable drug response or side effects. Some common drugs, including non-steroidal anti-inflammatory drugs, are metabolised by the P450 CYP2 C9 enzyme. There are mostly three variants of CYP2C9 gene which show alternated drug response. The variants *CYP2C9*1*, **2 *and **3 *occur most frequently with those of a caucasian background [50]. The enzymatic activity of **2 *and **3 *variant genes is decreased significantly, and carriers of the *3 variant are at risk for complications, such as bleeding after use of warfarin in small amounts [51]. Newer COX-2 inhibitors have less potential for causing gastrointestinal bleeding. The COX2 inhibitor etoricoxib has plasma protein binding of about 92% and is extensively metabolised, with only about 1% being excreted in urine as parent drug. CYP3A4 plays a major role in the metabolism of etoricoxib (60%), and CYP2C9, CYP2C19, CYP2D6 account for only a minor fraction ( 10%) of etoricoxib's metabolic profile [52]. Even though the pharmacokinetic profile is linear and in vitro studies support that etoricoxib does minor induction or inhibition of CYP isoenzymes, we want to test whether the mentioned CYPs or the polymorphisms of the MDR1 (e.g. C3435T) have a possible connection with the outcome of postoperative pain management.

## Study Design

We have chosen a 2 × 2 factorial design for the following reasons: the factorial design has several important features. Firstly, it has great flexibility for exploring the treatment effects in the trials. Whenever examining treatment variations, factorial designs are strong candidates as the design of choice. Secondly, factorial designs are efficient due to the ability to combine multiple studies into one rather than conducting a series of independent studies. Finally, factorial designs are the only effective way to examine interaction effects [53,54].

If the primary aim of a trial is to identify useful single treatments, then it could possibly be more cost effective to use a three-arm study than a 2 × 2 factorial design. In this trial, it is of interest to detect the treatment interaction, i.e. the opioid-sparing effect of a non-opioid treatment. The chosen study design has the power to identify such statistically significant differences between etoricoxibe and placebo treatments [55]. While the methods are developed for binary outcomes, they can be readily adapted to outcomes based on continuous, ordinal or time-to-event data using the methods for power calculation [55,56]. No attempt has been made to adjust for multiple comparisons. However, this can be achieved by simply changing the level of significance according to some recognised procedures such as the Bonferroni correction [55,57]. In our opinion, the study design allows to obtain specific results regarding the preemptive and postoperative analgesic effects of etoricoxib on (a) the cumulative morphine consumption and (b) other parameters as mentioned: predisposing characteristics influencing postoperative pain (inter alia by means of questionnaires), sensoric perception, genetic polymorphisms and others.

## Conclusion

This study is a large-scale randomised placebo-controlled trial to evaluate the efficacy of COX-2-inhibitors in preemptive and postsurgical pain therapy. It can be expected to provide new valuable information on clinical and pathophysiological effects in postoperative pain, i.e. a) the analgetic effectiveness of preemptive analgesia and b) its relation to e.g. sensoric perception or genetical predisposition as possible factors leading to persistent (chronic) pain.
